### Blinding

2.7

Practitioners will be informed whether their recruitment site has been assigned to IG or CG at the beginning of the study. Once a patient has been identified to be eligible for study participation and the family gave informed consent to participate, the practitioner will individually inform about the assignment to IG or CG. Evaluating data analysists at IMBE will be blinded and will receive blinded datasets only.

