### Study sample and setting

2.2

Adolescents aged 10 to 19 years (based on the WHO definition of adolescence) and their respective parents, i.e., caregivers, will be recruited for the study by their child and adolescent psychiatrists and/or psychotherapists. Recruitment sites will include 10 outpatient departments of participating clinics (five university hospitals, five large care clinics) and approximately 40 practices throughout Germany (coordinated via the Professional Association for Child and Adolescent Psychiatry, Psychosomatics, and Psychotherapy in Germany e.V., BKJPP).

All eligible recruitment sites will be assigned randomly to IG or CG. Sites randomized to CG will have the opportunity to use Res@t after study recruitment and follow-up are completed.

In addition to introducing the study in regular appointments, advertisements will be carried out via five health insurance companies and the German Society for Child and Adolescent Psychiatry, Psychosomatics, and Psychotherapy (DGKJP) who support the study. Adolescents and parents who are interested in the study will be referred to participating clinics and practices, an appointment for screening and diagnosis will be made, and they will be informed about study details.

Screening for DMUD will take place for all patients within regular child and adolescent psychiatric diagnostics. If a DMUD is confirmed during clinical examination, adolescents and parents will be informed verbally and in writing about the study purpose and procedure including intervention, assessments, and recruitment-site-associated randomized group allocation. Further information concerns confidentiality and data protection procedures including pseudonymization, anonymous data storage at the study center (German Center for Addiction Research in Childhood and Adolescence, DZSKJ, University Clinic Hamburg-Eppendorf, UKE) for 10 years after study completion, possible advantages and disadvantages of participation, and the option to withdraw from the study at any time and without any given reason. Before study enrolment, adolescents and parents give their informed consent and receive all necessary documents on the study.

Since all participants are patients in regular treatment, they will not be financially compensated. However, patients will be offered a voucher for a large selection of online shops as incentive for full questionnaire completion with graded values according to assessment points.

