### Randomization

2.5

A stratified cluster randomization will be employed, resulting in each recruitment site (outpatient department or practice) being randomly allocated to the intervention or waitlist control. Stratification is performed according to recruitment site size (annual patient number ≤ 600, > 600 and ≤ 1,600, and > 1,600) and location (urban or rural). An independent statistician at the Institute of Medical Biometry and Epidemiology (IMBE) at the University Medicine Hamburg-Eppendorf will randomly allocate recruitment sites using computerized random number generations within each stratum to IG or CG based on internal standard operating procedures, without knowledge of the identity of recruitment sites (with variable block length). Cluster randomization will be applied to avoid contamination between IG and CG conditions regarding TAU. Based on the resulting allocation, the intervention will be made available immediately (IG) or after the recruitment phase and follow-up data collection is completed (CG).

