### Assessment and data collection

2.6

Clinical assessments with the adolescents and respective parents will be realized at screening, baseline, week 10 (post-intervention), and week 20 (follow-up). By the latter, the durability of the treatment effect should be estimated. Screening and baseline visits should not be apart by more than 4 weeks, otherwise a clinical reevaluation will become necessary. In addition to clinical diagnosis and post-treatment evaluation, all assessments are performed digitally via standardized questionnaires, which are provided on an online platform without the involvement of the clinician. They will be automatically presented to the participants at the time points according to the study protocol. Participants will receive e-mail reminders just before and during the scheduled time frame. All data will be initially stored in a patient dossier on the ISO-certified e-mental health platform run by Embloom^1^ before pseudonymization and secure transfer to the central study center. Regular visits with the clinician will take place within TAU. These should support compliance and adherence to keep the drop-out rate as low as possible. Figure 1 shows all study phases including assessment time points. Table 1 shows all questionnaires and items used in the current study. Table 2 shows the schedule of the questionnaire application.

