	Family Communication Scale (FCS)	Family communication	10 Items	(51, 56)
	Patient Health Questionnaire-9 (PHQ-9)	Parental depression	9 Items	(57–59)
	Generalized Anxiety Disorder-7 (GAD-7)	General anxiety of parents	7 Items	(58, 60)
	Parenting Inventory – Revised (EEI-R)	Parenting style (without subscale about religion)	44 Items	(61)
	Questionnaire on Self-Efficacy in Parenting (FSW)	Parental self-efficacy	9 Items	(62)
	Perceived Stress Scale (PSS-10)	Psychological stress perception	10 Items	(47, 48)
	Ulm Quality of Life Inventory for Parents of Chronically Ill Children (ULQIE)	Quality of life of parents	29 Items	(63)
	Mindfulness Attention Awareness Scale (MAAS-5)	Parental mindfulness	5 Items	(53, 54)

**Table 2 tab2:** Diagram of trial activities and measurement time points.

	Study period								
	Enrollment			Intervention		Post-intervention and follow-up		Post-data collection	
Timepoint/Content	Screening (<4 weeks before baseline)	Baseline assessment (week 0)	Allocation	Res@t intervention (week 1–9 and week 15 [booster])	TAU	Post-intervention (week 10)	Follow-up (week 20)	Res@t intervention	TAU
*Enrollment*									
Eligibility screening	X								
Clinical assessment	X								
Informed consent	X								
Randomization IG/CG			X						
*Interventions*									
Intervention group (adolescent-parent dyads)				X	X				X
Waitlist control group (adolescent-parent dyads)					X			X	X
*Assessments*									
Adolescents						IG/CG	IG/CG		
Sociodemographics	X	X							
Media use	X								
GADIS-A	X					X	X		
SOMEDIS-A	X					X	X		
STREDIS-A	X					X	X		
SDQ	X					X	X		
PSQI		X				X	X		
ESS-CHAD		X				X	X		
PSS-10		X				X	X		
Family APGAR		X				X	X		
FCS		X				X	X		
MAAS-5		X				X	X		
Parents						IG/CG	IG/CG		
Sociodemographics		X							
Parental media use		X							
GADIS-P	X					X	X		
SOMEDIS-P	X					X	X		
STREDIS-P	X					X	X		
SDQ-f	X								
Media Rules		X				X	X		
Family APGAR		X				X	X		
FCS		X				X	X		
PHQ-9		X							
GAD-7		X							
EEI-R		X							
FSW		X				X	X		
PSS-10		X				X	X		
ULQIE		X				X	X		
MAAS-5		X				X	X		

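### Section 2.7 does not make disclosure of the arm wait for the week-0 questionnaires, so baselines of 13 secondary self-report scales can be collected after the family knows its arm

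*Protocol article*

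**What the plan says.** All references are to the protocol article.

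- **Section 2.7 (Blinding).** "Practitioners will be informed whether their recruitment site has been assigned to IG or CG at the beginning of the study". Once a patient is found eligible and "the family gave informed consent to participate, the practitioner will individually inform about the assignment to IG or CG". Eligibility and consent are the only conditions given.
- **Section 2.2.** "Before study enrolment, adolescents and parents give their informed consent".
- **Table 2.** Informed consent has a single mark, in the column that begins "Screening (<4 weeks before baseline". The next column begins "Baseline assessment (week 0". The row "Randomization IG/CG" is marked only in the Allocation column, which follows baseline.
- **Section 2.6.** "Screening and baseline visits should not be apart by more than 4 weeks"; a longer gap calls for clinical re-evaluation.
- **Section 2.5.** The unit of randomisation is the site, "resulting in each recruitment site (outpatient department or practice) being randomly allocated to the intervention or waitlist control".
- **Sections 1.1 and 2.10.1.** The primary contrast runs from screening to post-intervention.
- **Section 2.12.** Secondary endpoints are exploratory and are analysed by methods analogous to the primary model, which adjusts for the baseline score.

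**The concern.** In a cluster trial where the practitioner already knows the arm, the one thing that can still be controlled is when the family learns it. If the family hears at the screening visit that it gets the app now, or that it must wait, it then answers the week-0 questionnaires knowing this. Perceived stress, sleep, family functioning, parental self-efficacy and quality of life are all self-reported, and relief or disappointment could plausibly move some of them. A starting value that has already reacted to the allocation is no longer a pure pre-treatment measure. Adjusting for it, or subtracting it, carries that reaction into the estimated group difference. It cannot be repaired afterwards, because these scales have no earlier measurement.

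**Working it through.** No figure in the plan is at issue, so the check compares the order of events and counts the measures exposed.

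**1. Order of events**

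| Step | Section 2.7, with consent where Table 2 puts it | Table 2 columns read left to right |
|---|---|---|
| 1 | Site allocated, practitioner told | Screening and consent |
| 2 | Screening and consent | Week-0 questionnaires |
| 3 | Family may be told its arm | Randomisation |
| 4 | Week-0 questionnaires, up to 4 weeks after screening | Intervention or waiting |

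The randomisation mark in Table 2 cannot be a draw made after baseline. Section 2.5 randomises sites, and section 2.7 has practitioners informed at the start. At most, the mark stands for the moment when the family is told, but the table does not say so.

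**2. Measures exposed (Table 2)**

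First taken at week 0 and repeated at weeks 10 and 20:

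- Adolescents: PSQI, ESS-CHAD, PSS-10, Family APGAR, FCS, MAAS-5, which is 6.
- Parents: Media Rules, Family APGAR, FCS, FSW, PSS-10, ULQIE, MAAS-5, which is 7.
- Total: 6 + 7 = 13.

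Taken at week 0 only and named by construct in section 2.10.3 as covariates (parental distress, parenting style): PHQ-9, GAD-7, EEI-R.

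**3. Measures not exposed**

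GADIS, SOMEDIS and STREDIS (adolescent and parent versions), SDQ and SDQ-f are taken at screening. Section 2.3 makes reaching a cutoff on the adolescent or the parent symptom scale an inclusion criterion, so at least one version must be scored before eligibility, and hence before disclosure. The order of the remaining screening questionnaires relative to disclosure is not stated.

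**4. How a shifted baseline enters the estimate**

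Let δ be the difference between arms in the mean week-0 score that is caused by knowing the arm and has faded by week 10. Let ρ be the correlation between the week-0 and week-10 scores, with equal SDs at both times.

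- Baseline-adjusted comparison: bias = −ρ × δ. Using change as the outcome with baseline as a covariate gives the same group coefficient.
- Raw change score: bias = −δ.

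The document gives neither δ nor ρ. Purely as an illustration, with an assumed δ of 0.1 SD and ρ of 0.5, the adjusted bias is 0.5 × 0.1 = 0.05 SD in size. With the same δ it ranges from 0 (ρ = 0) to 0.1 SD (ρ = 1), and it is 0 if δ = 0. The sign depends on which arm shifts and which way. These values show the mechanism and are not an estimate for this trial.

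**The case against.** **The two places can be reconciled.** The word once in section 2.7 sets a precondition and names no day or visit. If the Allocation column is read as the point of disclosure, the order is consent, week 0, disclosure, and both places agree. This stands. A reader might infer that section 2.7 and Table 2 prescribe opposite orders, but the text does not go that far. What remains is that neither place states the rule, the row is labelled as randomisation, and a site that discloses at screening is complying with section 2.7.

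**It is visit-level detail that a condensed article may leave to the full protocol.** This stands only in part. The article does state when families are told, and that statement permits the unfavourable order.

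**The confirmatory analysis is untouched.** This stands for this route. The exposed endpoints are secondary and exploratory.

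**The gain is limited.** Families cannot be blinded to app versus waitlist, so the week-10 and week-20 self-reports are completed with the arm known in any case. Section 2.2 also has families informed of the site-based allocation procedure before they consent, by a practitioner who may already know the result. Later disclosure therefore cannot guarantee ignorance at week 0. This stands as a limit on the fix. It is not a reason to leave the baseline exposed, because an unbiased starting value is still worth having when later ratings are unblinded.

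**Conclusion.** The point holds as a gap in the disclosure rule together with a mislabelled row in Table 2. Followed as written, section 2.7 allows the only pre-treatment values of 13 self-report secondary scales, and three week-0 covariates, to be recorded after the family knows its arm. Baseline-adjusted exploratory comparisons on those scales can then be biased. The size and direction depend on how far knowledge of the arm moves the answers, and the document gives nothing from which to estimate that.

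Two stronger conclusions are tempting and are not supported:

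- *That the primary result is biased.* The primary scores start from screening, and this route does not reach them provided they are completed before disclosure.
- *That the bias is a stated share of the effect for which the trial is powered.* The standardised difference of 0.2 in section 2.4 is assumed for the primary hypotheses. Setting an assumed shift in secondary scales against it would compare different endpoints using invented inputs.

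This is a cheap improvement and not a threat to the confirmatory analysis.

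**What to change.** 1. In section 2.7, state that the practitioner tells the family its arm only after both adolescent and parent have submitted the week-0 questionnaires.
2. In Table 2, move site randomisation ahead of screening and relabel the column after baseline as disclosure of the arm to the family.
3. Time-stamp both the submission of the week-0 questionnaires and the disclosure, and report any baseline completed after disclosure.

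Cost: one sentence, a table correction and two time stamps; the questionnaires already run on a digital platform (section 2.6). The downside is that families learn their arm up to 4 weeks later than they would at screening. Because practitioners know the arm and cannot be blinded, the change lowers the chance that families know it at week 0 but does not exclude it.

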### Compliance

2.8

Compliance and adherence will be fostered by the treating clinician who observes the participants regularly within the context of normal treatment. Moreover, automatic reminders will be presented via the online app to the participating adolescents and parents. To all participants in the CG, the Res@t intervention will be offered after the completion of study recruitment. Incentives are planned for participants and clinicians to compensate for additional effort. These measures should increase study motivation and reduce drop-out rates.

### Res@t digital intervention

2.9

Res@t digital is the app-based translation of a manualized CBT-based treatment package comprising offline programs for adolescents with GD (Res@t–A *offline*) and their parents (Res@t–P *offline* (64)). A detailed description of the original program package and its further development can be found in a recent publication by Paschke et al. (22). For better readability, a short summary is given by:

Res@t was created within the theoretical framework of the Trias model of addiction (20) based on clinical experiences and up-to-date research findings on the etiology of DMUD and potentially effective treatment components. During the developmental process, qualitative interviews and focus groups had been conducted with clinical experts, affected adolescents, and their parents on needs and program requirements (26, 64). The findings were considered for the final Res@t version. Original content was adapted to fit digital demands, and specific elements for the treatment of SMUD and VSD have been added. Res@t digital is comprised of nine weekly sessions and one booster session in week 15 of approximately 20 min processing time each. Additionally, participants are encouraged to complete a daily calendar on usage times, non-digital activities, mood, and sleep.

Table 3 gives an overview of the Res@t session contents as offered to adolescents and parents. Modules with adaption to address the type of DMUD are indicated.

**Table 3 tab3:** Intervention modules^1^ in Res@t app training for adolescents and their parents.

Session (week)	Adolescents	Parents
1 (1)	Training start The first session presents the purposes and contents of the training and introduces the recurring exercises of self-monitoring and practicing mindfulness. At last, participants are asked to set up training goals, as well as a reward plan together with their parents.	Training start The first session presents the purposes and contents of the training and introduces the recurring exercises of self-monitoring and practicing mindfulness. At last, parents are asked to set up training goals, as well as a reward plan together with their child.
2 (2)^2^	Psychoeducation I^*^ Participants receive a normative comparison during a quiz on digital media usage patterns. They distinguish problematic from unproblematic behaviors in a swiping task and explore the (dis-)advantages of media use, using a four-field-table. Thus, motivation of change should be fostered.	Psychoeducation I^*^ Parents also receive a normative comparison on digital media usage patterns and distinguish problematic from unproblematic behaviors. Then, they get introduced to the assessment of disordered media use and are guided to take their child’s perspective on media use.
3 (3)	Psychoeducation II^*^ The vicious circle of addicted media use is presented and the participants create their personal explanatory model. Furthermore, they learn about the concept of self-control and assign self-control strategies to brief descriptions of distressed adolescents.	Psychoeducation II^*^ The vicious circle of addicted media use is presented to the parents and they learn about different influencing factors, before creating an individual explanatory model. Lastly, they also practice assigning self-control strategies.
4 (4)	Health and sleep hygiene Participants are quizzed about general health knowledge. They analyze their sleep quality, and receive psychoeducation on healthy sleep hygiene. Lastly, participants reflect on sleep hygiene strategies.	Communication Parents are introduced to the concepts of validation and I-messages and test their newly learned knowledge in playful exercises. Lastly, they are asked to practice in their day-to-day lives.
5 (5)	Self-care^*^ Participants are presented with (dys-) functional beliefs about media use and practice cognitive restructuring using so-called “firewall questions.” They explore their talents during a self-interview, and find alternative activities with the help of a decision tree.	Developmental tasks & parenting styles Parents get familiarized to the concepts of developmental tasks and are guided to distinguish the (dis-)advantages of different parenting styles. Lastly, they reflect on their personal situation.
6 (6)	Dealing with Emotions Participants are introduced to the ABC-model of Albert Ellis and practice building “emotional circuits” in an exercise. Furthermore, participants learn more about dealing with emotional distress using skills. Lastly, participants create their individual skills list.	Implementing rules Parents learn about the importance of rules and the differences of rules and requests. The implementation of rules is linked to the use of positive reinforcements, and parents reflect on their individual family rules.
7 (7):	Social relationships^*^ Participants are asked to differentiate the (dis-)advantages of real-life- compared to virtual (para-social) relationships. They are guided to build their individual social network and learn more about techniques to improve their real-life-relationships in a video.	Applying rules Parents explore the (dis-)advantages of rules and reflect on possible changes in their parenting. Furthermore, they are asked to conduct a “family council meeting” with their family.
8 (8)	Communication Participants are introduced to the concepts of validation and I-messages, before assembling the TOP-5 rules against bullying.	Family health Parents learn about stress perception and the influence of parental stress on family health. Also, they reflect on the different roles they exert in their lives and collect ideas on how to deal with stress.
9 (9)	Relapse Prevention^*^ Participants explore individual risk situations as well as warning signs of a possible relapse. Then, they are guided to create their personal list of self-control strategies.	Relapse Prevention^*^ Parents are guided to establish daily routines and alternative activities with their child. Then, they explore risk situations and build plans in case of a relapse. Lastly, parents explore their children’s talents to strengthen their positive mindset.
10 (15)	Booster Participants reflect on their progress and receive a recap-quiz on the contents of the training. Furthermore, they are re-introduced to the different exits of vicious circle of addicted media use. Lastly, participants evaluate their goal attainment.	Booster Parents reflect on their progress and receive a recap-quiz on the contents of the training. Furthermore, they are re-introduced to the different exits of vicious circle of addicted media use. Lastly, parents evaluate their goal attainment.

^1^Content is presented within four tasks per session (i.e., quizzes, psychoeducative videos, fill-in sections for personalized editing). After the first (introductory) session, each session follows the same structure. ^2^Starting with session two, participants are presented with a weekly summary of their calendar entries, self-reflect on their progress during the training, and practice mindfulness with the help of a video instruction at the beginning of each session. ^*^Content is targeted according to the focus on digital games/social media/streaming services.

The digital application in the adolescent and the parental versions will be made available via app stores. It is hosted in the secure Embloom platform environment. Based on the study arm allocation, the app, i.e., the intervention content, will be made available directly (for IG) or after individual data collection is completed (for CG). Figure 2 shows examples of the Res@t digital interface (in German language).

**Figure 2 fig2:**
[figure not shown]
Res@t digital dashboard. The dashboard of the German Res@t application includes an overview of weekly sessions and their completion. It organizes access to the diary, individual sessions, mindfulness exercises, and an emergency button with skills for acute stress reduction and contact numbers of the treating child and adolescent psychiatrist and psychotherapist as well as local emergency departments (left frame). The middle-left frame represents the graphical feedback of diary entries on the duration of digital media use, sleep, and other activities. A mindfulness exercise is shown in the middle right frame. The right frame depicts an example of a swiping task within a quest.

